Full Analysis Set(FAS): Per the Intention-to-Treat (ITT) principle, FAS includes participants who have received the herbal medicine preparation at least once and have had at least one measurement of the primary outcome measure

Safety Set (SS): Includes participants who have received the herbal medicine preparation at least once and have had at least one safety-related f/u

For demographic and baseline data, categorical data will be presented as n (%), and continuous data will be presented as mean±SD.

For efficacy parameters, continuous variables will be analyzed with paired t-test or Wilcoxon signed rank test, and categorical variables will be analyzed using the McNemar test or McNemar Exact test depending on their normality.

For safety parameters, adverse drug reactions (ADRs), SAEs, and serious ADRs will be presented as n (%), and differences across time points will be analyzed using the McNemar test or McNemar Exact test.

ANCOVA model will be used for analysis with sociodemographic factors that may affect HTN, such as sex, age, and use of antihypertensive drugs, included as covariates.

1. Withdrawal of consent and discontinuation
2. Discontinuation criteria

Participants may be discontinued from the trial in the following instances:

- Participants or their legal representatives requests discontinuation or participant withdraws consent due to unsatisfactory treatment effects during the study period
- Violation of inclusion criteria or meeting exclusion criteria
- Failure to take the modified SMS even once during the observational study period, despite giving consent and meeting eligibility criteria
- Occurrence of SAE related to the herbal medicine or AE making continuation in the study difficult
- Change of prescription during study
- Participant’s violation of study plan
- Lost to f/u during study period
- Other reasons due to which continuation of study is deemed inappropriate by the investigator

1. Study termination criteria

Upon occurrence of SAE suspected to be caused by the investigational drug, the PI notifies the joint IRB within 24 hours and terminate the study.

The clinical trial may be terminated prematurely in the following cases:

- Harmfulness of investigational product is discovered
- Moderate or severe AE deemed to have a relationship with the clinical trial occurred in more than 25% of the entire study population
- Study poses threat to the safety and well-being of study participants

1. Withdrawal of consent

Even after voluntarily consenting to participate, participants may withdraw their consent at any time without any disadvantages. If a participant wishes to withdraw their consent or meets the criteria for study discontinuation, their personal information and relevant data will be excluded from the analysis and will be discarded immediately.

1. Risks and benefits for study participants
2. Potential risks

The study lacks a control group, and only routine intervention and tests are involved; thus, there is no added risk from study participation.

During routine treatment, modified SMS has little risk for side effects or tolerance, but gastrointestinal symptoms (indigestion, heartburn) and autonomic nervous system symptoms (palpitations) may occur.

Since no additional interventions or tests are involved, there will be no cases of injuries caused by participation in the study. However, issues arising from routine medical care can be compensated according to the clinic’s malpractice liability insurance policy.

1. Potential benefits

Since the treatment protocol for modified SMS at Kyung Hee Bi, Che, Dam Korean Medicine Clinic is followed, there is no direct benefit to participants from participating in the study.

However, by participating in the study, participants contribute to gathering information on the effectiveness of modified SMS in improving HTN and observing its progress, which can aid in the future development of Korean Medicine-based treatments for HTN.

1. Risk/benefits analysis

Considering the potential risks and potential benefits, there is a low risk of side effects and no additional benefits to treatment. However, there are also no additional risks posed by study participation. Thus, the study is deemed to pose minimal risk to the participants.

1. Compensation for study participation

The compensation for the study participants (e.g., transportation) is 50,000 KRW for each visit (1, 2, 3) for a total of 150,000 KRW. Visit 4 is a telephone f/u, so there is no compensation.

Participants’ bank account numbers will be additionally collected for payment of the compensation.

1. Measures to protect participants’ safety and personal information
2. Information collected for routine medical care and patient management

Information collected for routine medical care and patient management includes personal information (name, resident registration number, email, phone number), demographic information (e.g., age, sex), medical history (e.g., past medical history, medication history, surgical history, family history), and various clinical outcomes (BP, height, weight, 3D blood pressure waveform test, EQ-5D-5L score). In addition, other details described in the observation items typically collected in Korean medicine practice [20] are collected. These do not deviate from the scope of information collected in routine medical care.

This study is a part of the national project commissioned by the NIKOM, and accordingly, study data collected according to the recruitment announcement will be documented and saved via eCRF (mytrial) established by the NIKOM and provided to the NIKOM. The data will only be provided to third parties or used for secondary research with the explicit informed consent of the participants.

1. Information additionally collected for study purposes

In addition to the information collected during routine medical care for study purposes, the participant’s bank account information will be additionally collected for payment of compensation.

1. Confidentiality

Personally identifiable data will be kept confidential, and participants will remain anonymous even when the results of the observational study are published. The details are as follows.

The investigators must be aware that upon the signing of the contract for this observational study, the Sponsor or auditor may review or copy the participant's charts and CRF for verification purposes.

1. Study data storage method and place

Relevant data will be stored in a locked, protected place (locked cabinet in the investigator’s office or password-protected computer) to ensure access to only permitted individuals.

In all study-related documents, participant identification codes (participant initials) will be used instead of their names.

1. Retention period

Personal information will be discarded three years after study completion

In accordance with Article 15 of the Enforcement Regulations of the Act on Bioethics and Safety, study data (IRB decision, written informed consent, personal information collection/use/provision status, study completion report) will be retained for three years after the study completion

1. Disposal method

In accordance with Article 15 of the Enforcement Regulations of the Act on Bioethics and Safety, personal information will be shredded immediately after study completion.

Study data will be shredded by a shredding service three years after completion of the study to prevent any leakage of information.

Information provided to the NIKOM via Mytrial will be retained for 10 years after study completion.

1. Monitoring

- Monitoring is performed to protect the rights and welfare of the participants, to ensure the reported clinical research data is accurate, complete, and verifiable against source documents, and to confirm that the trial is performed in accordance with the approved protocol, clinical trial management standards, and enforcement regulations. The monitoring is performed by a NIKOM-appointed monitor in the forms of regular site inspections or phone checks. During visits, monitors review participant records, inventory management records, and data storage (study files). The scope of monitoring activities includes ensuring compliance with the clinical trial protocol, checking for accurate and appropriate data collection, reviewing participant consent and re-consent forms, and reviewing collection and reporting of (serious) AEs and management of investigational products.
- Monitoring visits in this clinical study are categorized into initial, periodic monitoring, and end-of-study monitoring. The first monitoring visit occurs within 3 weeks after the enrollment of the first study participant. Periodic monitoring visits are scheduled based on the pace of participant recruitment, and end-of-study monitoring visit will occur after the end-of-study visit of the last participant. Additional monitoring visits may be conducted during the study period for purposes such as managing safety information, addressing low participant recruitment, or non-compliance with the study protocol or relevant regulations and guidelines.
- Monitors closely observe the progress of the clinical study and consult with investigators if any issues arise. The timing of their visits is coordinated between the investigators and the monitors. The investigators are also required to provide access to essential documents, such as participant source documents and basic study documents, as defined in the clinical study management standards and regulations, such that the monitors can verify the data entered in the CRF.

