[figure not shown]

Figure 3

Graphs summarize systolic BP(A), and diastolic BP(B) in groups of Nor, L-Con, L+mSaengmaeksan_W, and L+mSaengmaeksan_E. Treatment with mSaengmaeksan_E ameliorated HTN in the L-Congroup (a, ***p＜0.001 Norvs. L-Con; b, ***p＜0.001 L-Convs. L+mSaengmaeksan_E). Results are expressed as the mean ±S.E. (n=6 mice per group). Nor, normal; L-Con, L_NAME control; L+mSaengmaeksan_W, mSaengmaeksan water extract treated L-NAME control groups; L+mSaengmaeksan_E, mSaengmaeksan ethanol extract treated L-NAME control groups.

1. Purpose of study

This study is an exploratory observational study that aims to explore the safety and BP-lowering effects of modified SMS and to collect HTN-related clinical parameters by comparing before and after administration of modified SMS, an herbal medicine prepared and prescribed at Kyung Hee Bi, Che, Dam Korean Medicine Clinic for the treatment of HTN.

1. Names and positions of principal investigator, co-investigators, and sub-investigators
2. Principal investigator (PI)

| Name | Affiliation | Job position | Contact information | Roles |
| --- | --- | --- | --- | --- |
| [name] | Kyung Hee Bi,Che,Dam Korean Medicine Clinic | Director | [name] / [contact] | PI, recruit and enroll participants, provide information about study and obtain consent, collect data, measure observation parameters, and perform tests |

1. Co-investigators

| Name | Affiliation | Job position | | Contact information | | Roles | |  |
| --- | --- | --- | --- | --- | --- | --- | --- | --- |
| Name | Affiliation | | Job position | | Contact information | | Roles | |
| [name] | Kyung Hee Bichedam Korean Medicine Clinic | | Research assistant | | [name] / [contact] | | Study administration and trial assistance | |
| [name] | Korean Institute of Oriental Medicine | | Principal researcher | | [contact]/[contact] | | Study design | |
| [name] | Korean Institute of Oriental Medicine | | Principal researcher | | [contact]/[contact] | | Study design | |
| [name] | Korean Institute of Oriental Medicine | | Principal researcher | | [contact]/[contact] | | Develop data analysis and statistical analysis methods | |
| [name] | Korean Institute of Oriental Medicine | | Technical researcher | | [contact]/[contact] | | Monitors | |

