| [name] | Wonkang University College of Korean Medicine | | Assistant professor | | [name] / [[contact]](mailto:[contact]) | | Study design and data analysis consultatio | |
| [name] | Wonkang University College of Korean Medicine | | Graduate student  (Master’s) | | [name] / [[contact]](mailto:[contact]) | | Assist in study design and data analysis | |

1. Roles by affiliation

* Kyung Hee Bi,Che,Dam Korean Medicine Clinic: recruit participants, collect informed consent, perform trial

* Korean Institute of Oriental Medicine: study design and analysis, monitoring, administration

* Wonkang University College of Korean Medicine: study design and data analysis consultation

1. Name and address of trial facility

Trial facility (single-center study): Kyung Hee Bi, Che, Dam Korean Medicine Clinic ([name])

1. Sponsor

National Institute for Korean Medicine Development ([name])

1. Study period

Anticipated study period (1 year from approval by joint IRB. Scheduled to be completed on August 31, 2024)

1. Study participants
2. Recruiting facility

(Single-center) Kyung Hee Bi, Che, Dam Korean Medicine Clinic

1. Number of patients to be recruited

After screening candidates for eligibility, 30 participants who received mSMS will be recruited.

Study participants must meet all of the inclusion and not meet all of the exclusion criteria to be enrolled in the study.

1. Inclusion criteria
2. Adult men and women aged 19–74 years.
3. BP measured from the reference are at time of screening:

- If not taking antihypertensive drugs: 140 mmHg ≤ MSSBP(mean sittingSBP) < 180 mmHg
- If taking antihypertensive drugs: 130 mmHg ≤ MSSBP(mean sitting SBP) < 180 mmHg

1. Voluntarily provide a fully informed consent to provide medical records and personal information for use in the study.

- (*Reference arm is selected based on the process outlined in “12. Observation parameters-B.Measurement items”)
- (*Mean seated BP is defined in “12. Observation parameters-B.Measurement items)

1. Exclusion criteria
2. ≥ 20 mmHg difference in Systolic Sitting Blood Pressure (SSBP) and more than a 10 mmHg difference in Diastolic Sitting Blood Pressure (SDBP) across three consecutive measurements, taken at least 2 minutes apart in both arms
3. Mean seated SBP (MSSBP) ≥ 180 mmHg or mean seated DBP (MSDBP) ≥ 110 mmHg in the reference arm at time of screening

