4. Liver disease or kidney disease requiring treatment
5. Secondary hypertension
6. History of severe CVD: e.g., myocardial infarction, angina, severe arrhythmia
7. Diagnosis of psychiatric disorder or treatment for psychiatric disorder, including depression, within 2 months of visit
8. Other reasons that contraindicate use of modified SMS as determined by the clinician

- (*Reference arm is selected based on the process outlined in “12. Observation parameters-B.Measurement items”)
- (*Mean seated BP is defined in “12. Observation parameters-B.Measurement items”)

1. Control group

A prospective single-group preliminary observational design; there is no control group, and blinding and randomization are not applicable.

1. Anticipated sample size and grounds for sample size determination

This is an exploratory preliminary prospective observational study. In general, preliminary studies require a minimum of 12 participants [9]. In the present study, we aim to obtain data from 30 participants.

F/u is performed every 4 weeks. In general, 67% of participants re-visit the facility on week 4.

To obtain data from 20 participants with a potential 33% dropout rate, **30 participants** are required.

Every month, about 10 patients take modified SMS, so recruiting the target sample size within the study period is feasible.

In preliminary studies, a minimum of 12 participants are generally required. **Given that this study is a preliminary study collecting exploratory data for subsequent studies, as opposed to a study investigating the therapeutic efficacy, recruitment of 30 participants in consideration of potential dropouts is deemed adequate.**

1. Participant recruitment

Participants will be recruited among patients who visit the Kyung Hee Bi, Che, Dam Korean Medicine Clinic and based on the clinician’s assessment and patient consent.

To ensure consistency of recruitment and fairness for potential participants, a recruitment announcement containing the overall information about the study, including its purpose, inclusion and exclusion criteria, and study schedule, will be posted on the bulletin board within the clinic for a specified period. Visitors to the healthcare facility interested in participating in the study can contact via the contact details listed in the announcement or by directly contacting the research team (PI and co-investigators).

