- The study is conducted under a national research and development project commissioned by the National Institute for Korean Medicine Development (NIKOM) (evidence-generating research as part of Korean medicine innovative technology development project). The research data collected according to the study announcement will be recorded and stored through E-CRF (Mytrial) established by NIKOM and provided to them. Provision of the study data to a third party and use of the data for secondary studies will be permitted only after obtaining a separate consent from from the participants for the purpose.

1. Method
2. Outline of method
3. Study period

Anticipated study period (1 year from approval date. Scheduled to be completed by August 31, 2024)

1. Study site

Kyung Hee Bi, Che, Dam Korean Medicine Clinic; a prospective observational study on patients

1. Study design

Single-group, prospective, exploratory, preliminary observational study

This study is an observational study for preliminary exploration of the therapeutic effects of modified SMS on HTN and for exploration of feasibility for future randomized controlled trial.

1. Study schedule (standard management protocol): 4 clinical assessments

Baseline (wk 0, screening and enrollment, visit 1)

Mid-treatment (4 weeks after beginning dosing of modified SMS) (visit2)

End of treatment (8 weeks after beginning dosing of modified SMS) (visit3)

4-week f/u after treatment (12 weeks after beginning dosing of modified SMS) (visit4)

1. Standard protocol for modified SMS

The participants will undergo the following process per the standard protocol:

When using modified SMS, those receiving any other KM treatments, including acupuncture, pharmacopuncture, and moxibustion, will be excluded

1. Standard herbal medicine prescription protocol

- Compliance with pre-visit instructions:
  After making an appointment for the visit, patients are instructed to fast for 8 hours before the visit, refrain from smoking, drinking, and consuming caffeine the day before the visit, and to visit the clinic between 8–12 AM.
- History taking
- 3D BP waveform test (3-d pulse imaging study), blood test
- Same tests performed at F/u on weeks 4, 8, and 12 after herbal medicine prescription

1. Standard protocol visits

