- (Visit) Patients who take herbal medicine prescribed by Kyung Hee Bi, Che, Dam Korean Medicine Clinic are instructed to make f/u visits every 4 weeks for monitoring of AEs and clinical progress. In case of AEs, additional visits may be necessary.

1. Standard protocol tests

- The Standard management protocol at Kyung Hee Bi, Che, Dam Korean Medicine Clinic involves performing 3D BP waveform test and blood tests on patients taking herbal medicines every four weeks. In the present study, only patients taking modified SMS were enrolled. However, additional tests may be performed in cases of AEs.

1. Study intervention: administration of modified SMS per standard protocol

In the present study, we modified the traditional SMS formula used for CVD (ginseng, Ophiopogon japonicus, and Schisandra chinensis) based on clinical experience, classic texts, and experiment findings. We removed ginseng and added Platycodon grandiflorus and Pueraria lobata as well as Dioscorea opposita and Coix lacrymajobi to stimulate digestive functions. The formula consisting of **Pueraria lobata (5.33g), Platycodon grandiflorus (5.33g), Ophiopogon japonicus (5.33g), Dioscorea opposita (2.67g), Coix lacrymajobi (2.67g), and Schisandra chinensis (2.67g) (total 24g; unit g/day)** is referred to as saengmaeksangagambang (modified SMS). This is one of the unique empirical prescriptions used at Kyung Hee Bi, Che, Dam Korean Medicine Clinic. Although in actual practice at Kyung Hee Bi, Che, Dam Korean Medicine Clinic, **certain ingredients may be removed, doses may be adjusted, or other interventions such as acupuncture, may be added depending on the symptoms and disease being treated, such cases were excluded from the analysis in this study.**

- Patients take a 60-mL 70% alcohol-soaked decoction of the modified SMS formula prepared by Kyung Hee Bi, Che, Dam Korean Medicine Clinic twice daily before meals or between meals
- Dispensing of medicine on Visit 1, Visit 2: [number of days until next scheduled visit date (standard 28 days, maximum 35 days) + 3 days]* 2 packs. A standard of 62 packs, up to 76 packs, are packaged in a box or pack, labeled with the patient’s information.
- Participants will return unused medicine at the subsequent visit.
- Returned unused medications will be stored separately for each patient in a box/pack.
- At completion of trial, returned medicines will be disposed of following the facility’s medication disposal procedures.

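### Eligibility requires neither a stable antihypertensive regimen nor absence of recent modified SMS before visit 1, so the before-after change in MSSBP cannot isolate the product's effect

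*Protocol*

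**What the plan says.** The Purpose of study section sets out to explore safety and BP lowering "by comparing before and after administration of modified SMS". Under Primary outcome (section 13) this becomes the change in MSSBP from visit 1 to visit 3, with a null and an alternative hypothesis. Section 16 tests it two-sided at 5% by paired t-test or Wilcoxon signed rank test. The Control group section says that there is none.

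The inclusion criteria set the BP range by current drug use: "If not taking antihypertensive drugs: 140 mmHg ≤ MSSBP(mean sittingSBP) < 180 mmHg" and "If taking antihypertensive drugs: 130 mmHg ≤ MSSBP(mean sitting SBP) < 180 mmHg". The exclusion criteria contain one look-back window, and it concerns something else: "Diagnosis of psychiatric disorder or treatment for psychiatric disorder, including depression, within 2 months of visit". The schedule has a single entry visit: "Baseline (wk 0, screening and enrollment, visit 1".

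On modified SMS, the section on the number of patients says "30 participants who received mSMS will be recruited", and Standard protocol tests says "In the present study, only patients taking modified SMS were enrolled". Concomitant treatment during the regimen is unrestricted and documented. Medication history is taken at visit 1. Changes to it are collected at visits 2 to 4.

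**The concern.** In a one-arm study, visit 1 is the only comparator. The change to visit 3 reflects modified SMS only if nothing else that moves BP is still taking effect at visit 1, and only if the product is not already acting then.

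The criteria secure neither condition. A patient whose antihypertensive drug was started or increased shortly before visit 1 qualifies, and the rest of that drug's fall is counted as change on modified SMS. A patient whose drug was recently reduced or stopped also qualifies, and a rise from that would hide a product effect. A patient who recently finished a course of modified SMS and now restarts meets every criterion too, and part of the effect may already be in the baseline.

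The protocol intends these data to inform later studies and the feasibility of a randomised trial, so a distorted estimate would carry forward.

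**Working it through.** **The protocol's own figure.** The only sample-size arithmetic is 20 evaluable participants at 33% dropout: 20 / (1 − 0.33) = 29.85, rounded up to 30. This reproduces and does not depend on the present point. No effect size, SD or power is stated, so there is no power figure to check.

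**Does another part of the protocol close the gap?**
- *Run-in or washout:* none, because screening, enrolment and baseline are the same visit.
- *History taking (section 12):* covers antihypertensive use, dosage and dosage changes, but specifies no date of last change before visit 1.
- *Table 2:* from visit 2 on, it collects changes arising since the visit. A change made just before visit 1 is not one of these.
- *Covariates (sections 13 and 16):* sex, age, BMI, duration of HTN, comorbidity, initial BP, antihypertensive use and drug types. None measures how recent a start or change is.
- *Exclusion of other Korean medicine treatments:* applies while modified SMS is being used, not before.

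**Size of the shift.** The documents give no shares and no drug effects, so every value below is an assumption. If a share f of participants has a further change d from another drug, and the product effect is zero:

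mean shift = f × d

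- Low end: 0.10 × 8 = 0.8 mmHg
- High end: 0.30 × 10 = 3.0 mmHg

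A recent reduction or stop with a rise of the same size gives the same shift with the opposite sign. If a share f already has the full modified SMS effect at visit 1, the measured effect is (1 − f) times the true one: 0.9 of it at 10% and 0.7 at 30%.

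**Consequence for the planned test.** A two-sided 5% paired t-test was simulated with 40,000 runs per setting, at n = 20 (the evaluable target) and n = 30 (the number recruited), with an assumed SD of change of 10 or 15 mmHg. With no product effect and no one affected, about 5% of runs are significant. With no product effect and a share f falling 10 mmHg from another drug:

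| f | n = 20, SD 10 | n = 20, SD 15 | n = 30, SD 10 | n = 30, SD 15 |
|---|---|---|---|---|
| 10% | 6.6% | 5.9% | 8.0% | 6.2% |
| 25% | 16.4% | 10.2% | 22.8% | 13.6% |
| 50% | 48.1% | 27.2% | 65.7% | 38.4% |

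With a fall of 5 mmHg instead, the range across these settings is 5.1% to 25.0%.

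In the other direction, take an assumed true effect of −8 mmHg and a share f already at full effect. At n = 20 and SD 10, the mean change shrinks from −8 to −7.2, −6.0 and −4.0 mmHg at f = 10%, 25% and 50%. Power falls from 93% to 84%, 67% and 35%. At SD 15 it falls from 62% to 52%, 38% and 19%.

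**The case against.** The strongest reply is that this is an observational record of routine care. The protocol says that it is not meant to establish efficacy and acknowledges that conclusions are limited without a control group. Open entry is a legitimate pragmatic choice, and nothing shows that any participant would be affected. Antihypertensive use and dosage are recorded and adjusted for, and the case report form, which is not shown, may hold dates.

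Much of this stands. It lowers the weight of the point and makes the magnitudes illustrative. It does not remove the point: the primary outcome still has a formal hypothesis test, the acknowledged limitation concerns the missing control group rather than the baseline, and no named covariate measures recency.

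A reader might also infer that the study draws on existing users of modified SMS, so that it enrols people who already tolerate the product and understates adverse events. The protocol does not support that. Recruitment is among clinic visitors, consent and enrolment are at the initial visit, dispensing begins at visit 1, and later visits are counted from the start of dosing. All of this points to new starters. The sentence "In the present study, only patients taking modified SMS were enrolled" follows a description of tests for herbal-medicine patients in general and can be read as separating modified SMS patients from the others. The remark "Every month, about 10 patients take modified SMS, so recruiting the target sample size within the study period is feasible" is a feasibility count and does not say that those patients are prior users. What stands is narrower: no criterion rules out current or recent use, and two sentences are loosely worded.

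**Conclusion.** The point holds as a gap in eligibility, and closing it is a cheap improvement. As written, the plan can credit another drug's effect to modified SMS or hide an effect of modified SMS, and the planned covariates do not repair this.

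Two stronger readings should be avoided. One is that the comparison simply misses the product's effect. That fits prior modified SMS use, or a recent reduction or stop of an antihypertensive; a recent start or increase acts the other way and favours the product. The other is that the baseline ought to be untreated. The design deliberately admits treated patients with their own BP limit. What is lacking is a stable background and freedom from recent modified SMS. Entry of current users is possible, not established.

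The size is unknown from the documents. The shift of 0.8 to 3.0 mmHg rests on an assumed 10% to 30% affected and an assumed drug-driven fall of 8 to 10 mmHg. The simulated error rates and power rest on assumed SDs of 10 and 15 mmHg as well as assumed shares and effects. If no one is affected, this bias is zero.

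**What to change.** Add two eligibility lines: any antihypertensive regimen has been unchanged, and modified SMS has not been taken, for intervals before visit 1 that the sponsor sets. These lines define who is studied and ask no one to delay or alter treatment.

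If the sponsor prefers open entry, record at visit 1 the dates of the last antihypertensive start, change or stop and of the last modified SMS use. Then pre-specify a supportive analysis of the primary change in participants whose baseline is stable and free of modified SMS.

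In either case, reword the sentences under Number of patients to be recruited and Standard protocol tests, and the repeat of the latter under Additional interventions, visits, and tests. They should agree with the pre-dose baseline that the consent section and the schedule imply.

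The cost of the first option is a few otherwise eligible patients not enrolled. The cost of the second is two date fields and a supportive analysis on fewer participants.
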